### Recruitment and data collection

This is a multicenter, bidirectional cohort study. Eligible participants will be consecutively enrolled from nephrology and internal medicine departments across seven hospitals in Beijing. Retrospective data extraction will be performed only at the coordinating center (Beijing Chaoyang Hospital), while all participating centers will contribute prospective data collection. Pre-admission and admission-related baseline data, including demographic, clinical, and laboratory characteristics, will be retrospectively extracted from the electronic medical records (EMRs) at the coordinating center for eligible historical cases, while baseline standardized assessments will be prospectively performed at hospital admission for newly enrolled participants across all participating centers starting on January 3, 2025. During the prospective data collection phase, each participant will undergo standardized assessments encompassing: structured questionnaires for demographics, comorbidities, physical examinations and anthropometric measurements; laboratory tests including blood and urine biochemistry, inflammatory and metabolic indicators; geriatric assessment scales, frailty, cognition, nutrition, psychological state, physical performance. Collected variables were categorized into two groups: routinely available clinical indices (demographics, medical history, anthropometric measures and laboratory tests) and non-clinical indices, defined as non-routinely acquired geriatric assessment data (frailty scales and cognitive, functional, nutritional, and psychological assessments), which require specialized evaluation and are resource-intensive in routine clinical practice. All data will be entered into a harmonized electronic case-report form (eCRF). The database will be centrally curated at Beijing Chaoyang Hospital, following prespecified data quality control and harmonization procedures described below.

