## Methods

### Study design

A multicenter bidirectional cohort study is being conducted from December 1, 2024, to December 31, 2028 (Fig. 1). Beijing Chaoyang Hospital serves as the coordinating center, with six participating sites across tertiary and community hospitals. Both retrospective data extraction and prospective recruitment will be employed to establish a bidirectional cohort integrating hospital and community populations. Ethical approval has been obtained from the Institutional Review Board of Beijing Chaoyang Hospital (No. 2024-Science-914). All participants will provide written informed consent. The trial adheres to the Declaration of Helsinki and SPIRIT 2023 guidelines.

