### Validation and evaluation

Internal validation, 70% of data used for model training and 30% for testing within the Chaoyang Hospital dataset. External validation, independent testing using data from six partner centers. Performance metrics, AUC, calibration curve, Brier score, and decision-curve analysis. Model explainability, assessed using SHAP-based feature attribution and causal-effect visualization to ensure interpretability and clinical credibility.

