### Missing data

Multiple imputation by chained equations (MICE) will be applied under the missing-at-random assumption. Sensitivity analyses will verify robustness.

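### No source of FRAIL or geriatric data is named for the historical Chaoyang cases, yet training and internal testing use Chaoyang data and the MICE rule has no exception

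*Protocol article*

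**What the plan says.** The section Recruitment and data collection describes two data streams. Historical cases come from the coordinating center alone. Their pre-admission and admission data, "including demographic, clinical, and laboratory characteristics, will be retrospectively extracted from the electronic medical records (EMRs) at the coordinating center for eligible historical cases". For the other stream, "baseline standardized assessments will be prospectively performed at hospital admission for newly enrolled participants across all participating centers starting on January 3, 2025". The frailty, cognitive, nutritional, psychological and physical-performance scales are listed after the words "During the prospective data collection phase, each participant will undergo standardized assessments encompassing". The same section describes these scales as "non-clinical indices, defined as non-routinely acquired geriatric assessment data (frailty scales and cognitive, functional, nutritional, and psychological assessments".

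Other sections then use the data as follows:

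- **Primary outcome:** frailty is a FRAIL score of 3 or more.
- **Knowledge-distillation-based model optimization:** the teacher takes clinical and non-clinical indices; the student takes clinical indices only.
- **Validation and evaluation:** "70% of data used for model training and 30% for testing within the Chaoyang Hospital dataset". The six partner centers are used for external testing.
- **Missing data:** "Multiple imputation by chained equations (MICE) will be applied under the missing-at-random assumption". Unspecified sensitivity analyses are promised. No variable, cohort or data block is excepted.
- **Sample size justification:** 1,500 participants and about 300 frailty events, from 20% prevalence, about 30 candidate predictors and at least 10 events per variable.

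The article does not say how many historical cases there will be, where their FRAIL scores would come from, or what part they play in the modelling.

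**The concern.** A supervised frailty model needs a frailty label for each person it is trained or tested on. The protocol describes no way for a historical case to have one, and its own premise is that routine records often lack these assessments. All historical cases fall in the one center that supplies the training and internal-test data.

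That leaves two readings, each with a cost. If the missing-data rule is applied as written, the FRAIL outcome and the whole non-clinical block are filled in for these cases, in both the 70% and the 30% sets. The gap is then set by cohort membership and is not sporadic. Test labels generated from the same predictors let the model be scored partly against the imputation model. If instead these cases are left out of supervised work, the 1,500 and about 300 events overstate the labelled data to the extent that historical cases are counted in them. At stake are the credibility of the internal AUC and calibration, and the sample-size claim.

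**Working it through.** **1. The plan's own figures reproduce.**

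- Events per variable: n = 10 × 30 / 0.20 = 1,500; events = 1,500 × 0.20 = 300.
- Precision: half-width = 1.96 × √(0.20 × 0.80 / 1,500) = 2.02%, which matches the stated ±2% after rounding.

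Both figures require an observed FRAIL score for all 1,500.

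**2. Effect on the count if historical cases lack FRAIL.** Let h be the share of the 1,500 who are historical and have no FRAIL score. The protocol does not give h; the values are assumed. Labelled n = 1,500(1 − h), events = 0.20 × labelled n, events per variable = events / 30, half-width = 1.96 × √(0.16 / labelled n).

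| h (assumed) | Labelled n | Events | Events per variable | Half-width |
|---|---|---|---|---|
| 0% | 1,500 | 300 | 10.0 | 2.02% |
| 10% | 1,350 | 270 | 9.0 | 2.13% |
| 25% | 1,125 | 225 | 7.5 | 2.34% |
| 50% | 750 | 150 | 5.0 | 2.86% |

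**3. The loss falls on the training set.** Suppose Chaoyang supplies half of the 1,500, that is 750 (assumed). Training uses 0.70 × 750 = 525 people, with 525 × 0.20 = 105 events and 105 / 30 = 3.5 events per variable when every FRAIL score is observed. If half of the Chaoyang cases are historical without FRAIL, 52.5 observed events remain, or 1.75 per variable. The drop from 10 to 3.5 comes from the site and 70/30 splits and is a separate matter; only the step from 3.5 to 1.75 belongs to this point.

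**4. Effect on internal validation if the outcome is imputed.** Simulation inputs:

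- from the protocol: 30 predictors, 20% frailty, 70/30 split;
- assumed: 750 Chaoyang cases, AUC of 0.75 for the true risk, no FRAIL score in any historical case, historical share as shown (here a share of the Chaoyang cases, not of the 1,500).

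Missing labels were drawn from an unpenalised logistic imputation model fitted to the labelled cases, with a parameter draw. An unpenalised logistic model was then fitted to 525 and tested on 225. Reported AUC is taken on that partly imputed test set, true AUC on new cases with real labels. There were 150 replicates per setting.

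| Historical share of Chaoyang (assumed) | Reported AUC | True AUC | Gap |
|---|---|---|---|
| 0% | 0.71 | 0.71 | 0.00 |
| 25% | about 0.73 | about 0.69 | 0.04 |
| 50% | about 0.77 | about 0.67 | 0.10 |

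Repeat runs agree to about 0.01.

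**5. Two comparisons that limit the result.**

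- *Imputation model.* With a ridge-penalised imputation model, reported AUC is 0.714 at 25% and 0.720 at 50%. True AUC at 50% is 0.671, so the gap is 0.720 − 0.671 = 0.049, about half of the unpenalised one.
- *Source of the fall in true AUC.* Training on labelled cases only gives true AUC 0.713, 0.703 and 0.682 at 0%, 25% and 50%. Training with imputed labels gives 0.713, 0.700 and 0.678. The fall is almost the same, so it comes from having fewer labels. What imputation adds is the rise in the reported figure.

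**The case against.** The strongest reply is that much of this is inference. Four stronger readings are tempting, and the article does not support them:

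- *Historical cases have no FRAIL or geriatric data.* The list of extracted data opens with *including*, so it is not exhaustive. Assessments that are not routine may still be on file for some patients. What the text supports is that no source is named.
- *The plan imputes its primary outcome.* The missing-data section does not say so. It names a method and an assumption without listing variables. Outcome imputation is what follows if the rule is applied without exception.
- *All teacher inputs would be imputed.* The teacher also uses clinical indices, which the records supply. Only the non-clinical block is in question.
- *Imputation makes the real model worse.* The labelled-only comparison shows nearly the same loss.

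It can also be said that an article leaves the imputation model to the analysis plan, that the Discussion has the teacher use comprehensive data when it is available, that Chaoyang also recruits prospectively, and that the partner centers, all prospective, would expose an inflated internal AUC.

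These replies narrow the wording but do not remove the point. The Discussion remark is not an operational rule. External testing would show a drop, but with mixed record and prospective data in training and only prospective data outside, its cause would be hard to separate from differences in data capture. And the mismatch is between things that the article does state: what is listed for historical cases, where training takes place, and a sample size that presupposes 1,500 FRAIL scores.

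**Conclusion.** The point holds in this form: the protocol names no source of FRAIL or geriatric data for historical Chaoyang cases, draws all training and internal-test data from Chaoyang, and makes no exception to MICE. As written, it would either impute the outcome in training and test data or fall short of its own labelled sample wherever such cases are counted.

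The shortfall is simple arithmetic once a historical share is assumed: any unlabelled case among the 1,500 takes events per variable below the plan's threshold of 10. The AUC inflation is conditional. It needs outcome imputation to take place, and its size depends on an assumed Chaoyang sample, an assumed historical share, a plain logistic model in place of the planned network, and an imputation model whose penalisation roughly halves the gap at 50%. The direction is secure under those conditions; the exact figures are illustrations. If every historical case included has a recorded FRAIL score, the outcome-imputation and event-count problems disappear, and the protocol need only say so.

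**What to change.** 1. Require an observed FRAIL score for entry to supervised training, the internal and external test sets, the prevalence estimate, and the 1,500-participant and 300-event count.
2. Do not impute FRAIL in any test set. Do not impute the geriatric block where it was never administered.
3. Fit MICE within the training data only.
4. State how many historical cases are expected and what they are used for. Those without FRAIL should serve only as unlabelled data, for example to describe case mix or as student distillation inputs. The latter works only if the teacher can produce an output without the geriatric block, so that must be specified too.
5. Restate labelled n, expected events and events per variable, in total and for the Chaoyang training set.

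Items 1 to 4 are changes of wording. The real cost is that the countable sample shrinks by the number of unlabelled historical cases. Recruitment is planned to run to the end of 2027, so the labelled target can still be protected. The rule does not recover the discrimination lost through having fewer labels; it makes the reported figure honest about it.

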**Methods:**

This multicenter bidirectional cohort study (ChiCTR2500095133) will recruit 1500 adults aged ≥ 60 years with CKD (KDIGO criteria) from seven Beijing centers. Collected data will include routinely available clinical indices (demographics, medical history, anthropometric measures and laboratory tests) and resource-intensive non-clinical indices derived from comprehensive geriatric assessment (frailty, cognitive, functional, nutritional, and psychological assessments). Frailty will be assessed using the FRAIL scale. Causal feature learning will identify determinants of frailty risk, while a teacher-student knowledge-distillation framework will optimize prediction using routinely available clinical data. Internal and external validation will examine model accuracy, interpretability, and clinical applicability.

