### Measurements

#### Primary outcome

Frailty status in elderly CKD patients is defined using the FRAIL scale (Fatigue, Resistance, Ambulation, Illness, and Weight Loss; total score ≥ 3 indicating frailty). The primary analytical objective is to examine associations between clinical and non-clinical indices and frailty status and to support the development of individualized frailty risk prediction models.

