**Fig. 2 Fig2:**
[figure not shown]
Overview of the proposed causal-learning and knowledge-distillation framework for frailty risk prediction and individualized intervention in elderly patients with CKD. Clinical indices represent routinely available clinical variables (demographics, medical history, anthropometric measures and laboratory tests), while non-clinical indices represent resource-intensive geriatric assessment data (frailty, cognitive, functional, nutritional, and psychological assessments). The full-indices model is trained using both clinical and non-clinical indices, whereas the clinical-indices-only model is optimized through knowledge distillation to enable frailty risk prediction and intervention decision support in data-limited clinical settings

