### Causal-learning-based frailty modeling

Patient-level clinical indices and non-clinical indices will first be processed using a structured modeling pipeline, as illustrated in Fig. 2. Raw input variables will be transformed into standardized feature representations through the patient information encoding module. These encoded features will then be input into the disease feature factorization module to generate latent disease-related feature factors. The extracted feature factors will subsequently be used for causal structure estimation.

Based on the learned feature relationships, a causal mask will be constructed to represent the dependency constraints among variables. This causal mask will be integrated into the downstream prediction network to guide feature interaction and information flow during model inference. Finally, the masked feature representations will be used as inputs to the prediction module to generate frailty risk estimates and intervention decision-support outputs for elderly patients with CKD.

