### Knowledge-distillation-based model optimization

A teacher–student learning framework will be implemented. The teacher model is trained using full indices including both clinical and non-clinical indices. The student model, restricted to routinely available clinical indices only, is trained by minimizing the distillation loss between teacher and student outputs, enabling the student model to learn compressed representations capturing information patterns related to geriatric assessment and frailty evaluation from routinely available clinical data. This strategy allows simplified deployment of the prediction model in routine clinical environments with limited data availability.

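### The FRAIL scale defines the outcome, yet frailty scales are listed among the inputs to the teacher model, the causal step and the primary association analysis

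*Protocol article*

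**What the plan says.** **Outcome.** Under Primary outcome, "Frailty status in elderly CKD patients is defined using the FRAIL scale", with a total of 3 or more counted as frail. The Methods paragraph of the Abstract names the same instrument: "Frailty will be assessed using the FRAIL scale". No other frailty instrument is named for collection.

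**Predictor groups.** Recruitment and data collection sorts the variables into two groups. The second is "non-clinical indices, defined as non-routinely acquired geriatric assessment data (frailty scales and cognitive, functional, nutritional, and psychological assessments". The Fig. 2 caption repeats this for the modelling framework: "non-clinical indices represent resource-intensive geriatric assessment data (frailty, cognitive, functional, nutritional, and psychological assessments". The Abstract also counts frailty among the non-clinical indices.

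**Use of the groups.**
- Primary outcome: the objective is to "examine associations between clinical and non-clinical indices and frailty status".
- Causal-learning-based frailty modeling: "Patient-level clinical indices and non-clinical indices will first be processed using a structured modeling pipeline", and the resulting factors go into causal structure estimation.
- Knowledge-distillation-based model optimization: "The teacher model is trained using full indices including both clinical and non-clinical indices". The student receives clinical indices only and "is trained by minimizing the distillation loss between teacher and student outputs".

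**Timing.** Outcomes and analysis states that the study has no follow-up endpoints.

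**The concern.** A predictor group that contains the outcome instrument leaks the label into the model. Three parts of the study are exposed:

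- **Teacher metrics.** AUC, calibration, Brier score and decision curves for the teacher would say nothing about what geriatric assessment contributes.
- **Distillation.** The teacher is meant to pass on information from cognitive, functional, nutritional and psychological assessment. A teacher that can read the label has no need of that information.
- **Determinants and association.** The first study aim is to identify key factors related to frailty. With the frailty scale among the candidates, the primary association objective partly relates a scale to itself, and attribution methods would favour that scale. The intervention suggestions come from the same modelling pipeline.

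**Working it through.** **1. The plan's own figures.** Sample size justification reproduces:
- Events per variable: n = 10 × 30 / 0.20 = 1,500, with 1,500 × 0.20 = 300 events.
- Precision: 1.96 × √(0.20 × 0.80 / 1,500) = 0.0202, which matches the stated ±2% after rounding.

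Neither figure depends on this point.

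**2. Tracing the definitions.**

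| Step | Section | Content |
|---|---|---|
| Label | Primary outcome | Y = 1 if FRAIL total S ≥ 3, otherwise 0 |
| Input group | Abstract; Recruitment and data collection; Fig. 2 caption | Non-clinical indices include frailty scales |
| Causal step | Causal-learning-based frailty modeling | Both groups enter |
| Teacher | Fig. 2 caption; Knowledge-distillation-based model optimization | Both groups enter |
| Association | Primary outcome | Both groups set against frailty status |
| Student | Knowledge-distillation-based model optimization | Clinical indices only |

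Nothing in the text takes FRAIL out of the inputs. With no follow-up endpoints, the frailty input cannot be an earlier measurement that predicts a later state.

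**3. What the inputs permit.** Suppose S, or all five items that sum to S, is entered.
- AUC = P(score of a frail patient > score of a non-frail patient) + ½ P(tie). Every frail patient has S ≥ 3 and every non-frail patient has S ≤ 2. Ranking on S therefore gives AUC = 1.00, whatever the prevalence or item correlations.
- Brier score = mean of (p − Y)². The rule p = 1 when S ≥ 3 and p = 0 otherwise gives 0. For comparison, predicting the assumed 20% prevalence for everyone gives 0.20 × 0.80 = 0.16.

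**4. Simulated illustration.** 200,000 patients, five binary items driven by one latent trait, outcome = total ≥ 3. The item correlations are assumptions, because the documents give none.

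| Assumed latent item correlation | Prevalence | AUC, FRAIL total | AUC, one item | AUC, non-frailty predictor correlated 0.5 with the trait |
|---|---|---|---|---|
| 0.3 | 0.197 | 1.000 | 0.764 | 0.691 |
| 0.5 | 0.199 | 1.000 | 0.805 | 0.717 |

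Only the column for the total is free of the assumed correlations. The last two columns show why an attribution method would favour frailty items over other predictors under such assumptions.

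**5. Consequence for distillation.** The student minimises a loss L(t, s) between teacher output t and student output s. As t approaches Y, L(t, s) approaches L(Y, s), which is ordinary training on the observed label. The teacher then adds little.

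**The case against.** **It is a data-collection taxonomy, not a predictor list.** The sentence under Recruitment and data collection sorts variables by how routinely they are acquired. The primary objective sets indices on one side and frailty status on the other. An itemised predictor list is something a journal article may leave to the full protocol. This has some force: it is not established that the teacher, once built, will contain FRAIL. It does not rescue the text. The Fig. 2 caption repeats frailty in the definition used for modelling and says that the full model is trained on both groups. The distillation section and the limitations in the Discussion also treat frailty evaluation as information that the student should recover. This is a stated input rule that includes the outcome, not an omitted detail.

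**The plural may refer to another instrument.** None is named for collection. A second frailty scale taken at the same visit would still be close to a duplicate of the outcome.

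**Stronger readings that the documents do not support.**
- *The teacher will certainly show AUC 1.00 and Brier 0.* These are what the inputs permit. The data also pass through encoding, latent factorisation and a causal mask, so a fitted model may fall short.
- *The deployed tool is circular.* The student's inputs exclude frailty scales, so testing it against observed FRAIL status is not directly circular.
- *Medical history, anthropometry, gait speed and chair-stand also leak the label, because they overlap with FRAIL items.* The article names the five items but does not say how they are scored. A correlated measurement is a legitimate predictor, not leakage.

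**Conclusion.** The point holds and should be corrected before models are built. As written, the label is a threshold of a variable that belongs to the teacher's inputs, to the causal-step inputs and to the predictors in the primary association objective.

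Its size is conditional. If the FRAIL total or all five items are entered, perfect teacher discrimination is attainable whatever the prevalence or item correlations. The loss falls on the teacher's metrics, the rationale for distillation, and the determinants and association results. If the teacher did collapse to the label, the student would be roughly a model trained on that label: the gain from distillation goes, but the tool is not invalidated.

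The conclusion assumes that the frailty scales in the non-clinical indices include FRAIL, the only frailty instrument named for the study.

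**What to change.** 1. Remove frailty from the definition of non-clinical indices in the Abstract, Recruitment and data collection, and the Fig. 2 caption.
2. State under Primary outcome, Causal-learning-based frailty modeling and Knowledge-distillation-based model optimization that the FRAIL total, its five items and any other frailty scale serve only as the outcome label. Exclude them from the association predictors, the causal-structure inputs and the teacher inputs.

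**Cost.** Wording only. No new data are needed, and the student's inputs stay as they are. The target of 1,500 can stand: under the plan's rule n = 10 × k / 0.20 = 50k, so each predictor removed from the count of about 30 lowers the minimum by 50. The downside is that teacher performance will look less favourable. Trial status anticipates final analyses by mid-2028, so the text can be corrected well before them.
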